#### Selection of indicators

The selection of quality indicators followed a three-step procedure. First, we searched the published and grey literature for frequently used diabetes quality of care indicators and population-based surveys exploring the quality of care of patients with diabetes. Then, we identified published clinical practice guidelines on diabetes care and considered those most recently updated and used by a group of regional partners adapting diabetes guidelines for Switzerland. The guidelines developed by the following agencies were considered: National Institute for Health and Clinical Excellence (NICE), Scottish Intercollegiate Guidelines Network (SIGN), International Diabetes Foundation (IDF), Canadian Diabetes Association (CDA), American Diabetes Association (ADA), Haute Autorité de Surveillance (HAS). Finally, we took into account three criteria: clinical significance, practical relevance (feasibility), and reliability/validity of the measurement. When several instruments existed, we considered their validity, their length, and the existence of a French version. We favoured instruments which presented the best balance of those latter criteria.

#### Primary outcomes: processes and outcomes quality of care indicators

We considered as primary outcomes all usually recommended diabetes processes-of-care indicators, as well as the following outcomes of care indicators: HbA1C levels, as an intermediary outcome associated with future development of diabetes complications [12–14], HRQoL and QoL as measured using a generic tool (SF-12) [15] and a diabetes-specific quality of life tool (Audit of Diabetes-Dependent Quality of Life 19 – ADDQoL) [16], respectively, and patient assessment of chronic care, i.e. how care is congruent with the Chronic Care Model (PACIC) [17, 18].

#### Exposure variables

In the 2012 baseline questionnaire, we also added a small number of questions regarding knowledge and participation in the few activities proposed that year by the PcD. These questions were only asked to patients recruited in 2012 in order to describe possible differences in terms of exposition to, and awareness of, the PcD, because patients were recruited over two different time periods.

#### Other variables of interest

The other variables of interest considered in the baseline questionnaire are briefly described thereafter; more details are provided in Table 1 and Additional file 1.Diabetes characteristics and related complications;Medication adherence using the Morisky medication adherence questionnaire [19];Healthcare utilisation within the past 12 months: ambulatory care visits, emergency visits, hospitalisation, home care services, domestic home support;Care foregone because of costs;Health status and health habits: anthropometric measures (weight and height allowing the calculation of the body mass index (BMI)), smoking status, alcohol consumption using the AUDIT-C questionnaire [20], levels of physical activity using questions from the Swiss Health Survey [21], depression screening using two validated questions [22] and comorbidities;Self-management activities and support measures: home glucose self-monitoring, HbA1C knowledge, participation in diabetes education classes, membership of the local diabetes association (Association Vaudoise du Diabète – AVD), knowledge of the “Diabetes Passport” (a small booklet with data, information and reminders) and if it was known, whether it was used;“Self-efficacy” measure, which was developed de novo because available instruments were either not appropriate from our point of view, or too long or did not have a French version. We were interested in exploring how easy/difficult it was for patients to manage their diabetes, overall, and also specifically, regarding the daily management of physical activity, medication and diet;Level and source of information about diabetes;Support and satisfaction from the healthcare team or from the members of the social network, if any;Overall satisfaction with current care and care recommendation to others;Patients’ socio-demographic characteristics: age, gender, nationality, place of residence, marital status, family size, education, employment, household income and insurance status.

#### Pretest of the questionnaire

Before the recruitment, we pretested the questionnaire among 12 patients with diabetes to ensure the understanding and acceptability of the instructions and of the questions, as well as to measure the completion time of the questionnaire as a whole.

### Treating physicians’ questionnaire

If participants agreed to share their physicians’ contact details, the physicians were contacted and asked to complete a questionnaire on their patients’ clinical, laboratory and processes-of-care values, as well as a personal questionnaire including some of their characteristics and characteristics of their practice (Table 2).

**Table 2 Tab2:** Overview of the variables, measures and instruments used in the Physician-completed questionnaires

Section	Variables	Details/Answers
*Patients’ information*		
Diabetes	Diabetes type	
Laboratory results	HbA1C, lipid profile, serum creatinine^a^, urine microalbuminuria, blood pressure, weight, height	Last value and date
Processes-of-care	Diabetic foot examination, eye examination by ophtalmologist, influenza vaccination	Done/not done and date
Global satisfaction with patient managment	Satisfaction with patients’ care and management, barriers to better care management	
*Physicians’ characteristics*		
Personal information	Age, gender, year of diploma, year of start of private practice, board certification type	
Practice information	Practice location, practice type, activity rate, participation in quality programmes/circles	

^a^Since the 2012 follow-up

#### Patients’ information

Physicians were asked to report the type of diabetes (type 1, type 2, other:specify), the last value and date of the following measures: HbA1C, lipid profile, serum creatinine (since the 2012 follow-up), urine microalbuminurie, blood pressure, weight and height. They were also asked to report whether the following processes-of-care were done or not as well as the date of the examination: foot examination, eye examination by ophthalmologist, influenza vaccination. Finally, they had to assess satisfaction with their patients’ care and management (5-point scale: entirely satisfied to not at all satisfied), as well as describe the barriers they were facing which prevented them to better take care of their patients (no barrier, insufficient time during consultation, other health problems of the patient, lack of motivation of the patient, health insurance reimbursement or insurance problem, language or cultural barrier, other).

#### Physicians’ characteristics

Physicians’ characteristics encompassed age, gender of the physician, year of medical diploma, year of start in private practice, and board certification type. We also asked a few questions allowing the characterization of their practice: location and type, activity rate, participation in quality programmes/circles.

### Follow-up

#### Follow-up process

Participants will be followed annually by mail questionnaires (information letter, paper questionnaire and prepaid reply envelope). To maximise retention of participants in the cohort, we will send a postcard reminder 2 weeks after the first mailing to non-respondents and a complete reminder package again 2 weeks later (questionnaire, information letter and prepaid reply envelope). Persistent non-respondents will be contacted by telephone; a minimum of three contact attempts over different days and times is planned.

Because of time constraints and overall limited participation to research projects, treating physicians will be contacted every 2 years only.

### Follow-up questionnaires

The core of the follow-up patients’ questionnaires will be similar to the baseline questionnaire, particularly with regard to the questions targeting primary outcomes, healthcare utilisation, health status and health habits as well as to the questions assessing knowledge and participation to PcD projects. According to the needs and specific interests of the PcD, new questions or thematic modules will be added to the follow-up questionnaires. In 2013 for example, a module on diabetic foot, as well as the Stanford self efficacy questionnaire and a health literacy question were added. In order to keep a questionnaire of a reasonable length, questions representing variables other than primary outcomes may be removed momentarily from the follow-up questionnaire.

The physicians’ questionnaire will be similar to the baseline one.

### Data entry and analysis

Upon receipt, questionnaires are first checked for obvious mistakes, and then scanned with an automated forms processing system, TeleForm™. Exported data are then systematically verified to detect errors. Patients’, physicians’ and pharmacies’ administrative data are kept in separate tables. A unique ID allows to link clinical and administrative information.

Descriptive analyses (univariate and bivariate) will be performed first. Then, depending on the research questions, appropriate statistical analyses will be conducted. Analyses, when appropriate, will take into account the hierarchical structure of the data (clustering by pharmacy and longitudinal design).

### Ethical considerations

The study protocol was approved by the Cantonal Ethics Committee of Research on Human Beings of the Canton of Vaud (Protocol N° 151/11). This study is registered with ClinicalTrials.gov, identifier NCT01902043. Informed consent was obtained from all participants, and data will be kept anonymous.

## Discussion

The implementation of CoDiab-VD followed a qualitative study on the evaluation of patients’ and professionals’ needs regarding the management of diabetes in this canton [23]. Both these first qualitative results and CoDiab-VD baseline quantitative results were, and will be useful for the adaptation of the PcD to the needs of healthcare professionals caring for patients with diabetes and other stakeholders. In addition, CoDiab-VD will be a helpful tool i) for the pragmatic evaluation of the PcD, and ii) for the future development and implementation of PcD projects.

One of our study design’s strength is the recruitment through community pharmacies [11], which allowed us to obtain a sample probably more representative of the population of patients with diabetes than a recruitment through medical practices or hospitals. In fact, we hypothesized that this method would limit the selection of patients on the basis of the level of care received, this information not being available to pharmacists. However, this hypothesis could not be confirmed by a comparison of participants’ and non-participants’ characteristics because data on non-participants could not be collected. Elements in favour of an acceptable representativeness are the fact that our study participants did not differ significantly from participants with diabetes of the CoLaus study [6], another population-based study conducted in the same region, regarding a few common characteristics (age, gender, education, smoking status, BMI) ([name], personal communication). The minor differences probably stemmed from the fact that the population of the latter cohort were limited to a narrower age range (35–75). Another positive aspect of the cohort CoDiab-VD is the fact that we collected at baseline, and plan to collect in the future, a broad range of quality indicators that include not only commonly considered processes-of-care but also a variety of patient-reported outcomes. In fact, the latter encompass different aspects of diabetes and diabetes care that are important to patients but nevertheless often neglected despite the fact that they represent important measures to take into account when wishing to capture the complexity of the quality of diabetes care [24–26].

The cohort CoDiab-VD is, however, subject to several limitations. First, the number of patients recruited was below the sample size calculated (inclusion of 519 participants instead of the planed 600). However, because of a greater number of clusters (pharmacies) than expected and a conservative sample size calculation, the precision around point estimates was nevertheless acceptable. This sample size is also large enough (power > 90 %) to detect a 0.5 % point decrease in HbA1C, a PCS or MCS change of 5 points, a PACIC change of 0.3, or an absolute change of process of care of 10 %. Second, one could criticize the choice of self-reported data for the majority of the outcomes, since they may be prone to recall bias – an inherent limitation of such data collection, or be over- or underestimated. Specific analyses, on a fraction of the cohort data, demonstrated a good agreement between patient- and physician-reported outcomes for simple processes-of-care, such as measurement of blood pressure, HbA1C, weight and lipid profile [27]. Physician-reported outcomes were asked for in a second phase. Since their collection was dependent on the physicians’ willingness to participate, these variables were only available for a fraction of the sample, about 50 % at both recruitments and first follow-up. We will nevertheless favour the collection of some physician-reported measures (i.e. blood pressure, HbA1C value) in the future because they are more accurate. Third, between the 2011 baseline recruitment and their first follow-up in 2012, 58 patients refused to continue to participate in the cohort, what could be explained by the lack of information of the 2011 initial group of patients about the annual follow-ups to come. Globally however, when considering patients both recruited in 2011 and in 2012, this amounted to only a tenth of the total baseline sample size. In addition, the comparison of characteristics of participants to the baseline and of participants to the 2013 follow-up did not highlight major differences.

CoDiab-VD will allow drawing a broad picture of patients with diabetes and their care over time. It will also contribute to the evaluation of the PcD and to support decisions about which targeted actions to implement.

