**Methods/Design:**

The cohort CoDiab-VD is a prospective population-based cohort study. Patients with diabetes were recruited in two waves (autumn 2011 - summer 2012) through community pharmacies. Eligible participants were non-institutionalised adult patients (≥18 years) with diabetes diagnosed for at least one year, residing in the canton of Vaud and coming to a participating pharmacy with a diabetes-related prescription. Women with gestational diabetes, people with obvious cognitive impairment or insufficient command of French were not eligible. Self-reported data collected, included the following primary outcomes: processes-of-care indicators (annual checks) and outcomes of care such as HbA1C, (health-related) quality of life measures (Short Form-12 Health Survey – SF-12, Audit of Diabetes-Dependent Quality of Life 19 – ADDQoL) and Patient Assessment of Chronic Illness Care (PACIC). Data on diabetes, health status, healthcare utilisation, health behaviour, self-management activities and support, knowledge of, or participation to, campaigns/activities proposed by the PcD, and socio-demographics were also obtained. For consenting participants, physicians provided few additional pieces of information about processes and laboratory results.

Participants will be followed once a year, via a mailed self-report questionnaire. The core of the follow-up questionnaires will be similar to the baseline one, with the addition of thematic modules adapting to the development of the PcD. Physicians will be contacted every 2 years.

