### Sample size

The number of patients with diabetes to include in the study was estimated to obtain good precision (i.e. confidence interval width) around the following primary outcomes at baseline: mean HbA1C value, mean Physical and Mental component scores (PCS and MCS) of the Short Form-12 Health Survey (SF-12), mean Patient Assessment of Chronic Illness Care (PACIC) global score, and percentage of patients receiving recommended annual processes-of-care. Considering the clustering of data by pharmacies (40 pharmacies, each recruiting 15 patients, intra-class correlation 0.05, alpha 0.05, beta 0.2), the recruitment of 600 participants was deemed appropriate. This sample size was also large enough to detect a 0.5 % point decrease in HbA1C between two time points. In addition, it was above the sample size required for such a change considering repeated measures within a same individual.

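### The attrition check compares baseline participants with a subset of themselves, so at low loss it cannot show that those who left resemble those who stayed

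*Protocol article*

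**What the plan says.** The third limitation in the Discussion of the protocol article concerns loss from the cohort. Between the 2011 baseline and the 2012 follow-up, "58 patients refused to continue to participate in the cohort". The article then sets this loss against both recruitment waves together and concludes that "this amounted to only a tenth of the total baseline sample size". As further reassurance it adds that "the comparison of characteristics of participants to the baseline and of participants to the 2013 follow-up did not highlight major differences".

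Two other statements fix what is being compared. The first limitation gives the baseline total: "inclusion of 519 participants instead of the planed 600". The abstract dates the recruitment: "Patients with diabetes were recruited in two waves (autumn 2011 - summer 2012) through community pharmacies". Nobody joined after 2012, so each person in the 2013 follow-up is also one of the baseline participants. The article names no group of leavers. It does not list the characteristics compared, and the text does not say how many took part in 2013 (the flowcharts are not shown).

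**The concern.** To learn whether loss was selective, one asks whether the people who left differ from the people who stayed. The comparison reported sets the whole against one of its parts. Because the stayers make up most of the whole, they appear on both sides and pull the two averages together. The smaller the loss, the stronger the pull. A finding of little difference is therefore weak evidence that leavers and stayers are alike.

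This matters because the cohort is meant to follow quality of care over time and to assess the cantonal programme, and no control group is described. If patients with worse control or worse care leave, a comparison of yearly averages can drift upward with no real change. If loss is related to how patients later change, within-person results are affected as well. A reader should know how far the reported check speaks to each of these.

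The article recognises the informative contrast elsewhere in the same section. On selection at recruitment, it says that participants could not be compared with non-participants because nothing was recorded on the latter. That obstacle does not apply to attrition, since leavers had been enrolled with a baseline questionnaire.

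**Working it through.** **Inputs**
- Baseline total: 519 (Discussion, first limitation).
- Documented leavers: 58, all from the 2011 wave (Discussion, third limitation).
- Number taking part in 2013: not in the text. Losses of 104 and 156 are assumed to span about 20% and 30%.
- Leaver/stayer gaps of 20 percentage points, 0.5 in HbA1C and 0.5 SD: assumed for illustration.
- Alpha 0.05 (Sample size: "intra-class correlation 0.05, alpha 0.05, beta 0.2"), taken as two-sided.

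**The article's own figure.** 58/519 = 0.112, or 11.2%. An exact tenth of 519 would be 52 patients, so a tenth is fair as a verbal rounding.

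**The identity.** Let d be the fraction lost. Then

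mean(all) = (1 − d) × mean(stayers) + d × mean(leavers),

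and so

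mean(all) − mean(stayers) = d × [mean(leavers) − mean(stayers)].

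This is exact and needs no distributional assumption, provided that baseline values are used for both groups.

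**Difference shown for a given true gap**

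| Lost by 2013 | d | 20 points shows as | 0.5 HbA1C shows as | 0.5 SD shows as |
|---|---|---|---|---|
| 58 (documented) | 0.112 | 2.2 | 0.06 | 0.06 |
| 104 (assumed) | 0.20 | 4.0 | 0.10 | 0.10 |
| 156 (assumed) | 0.30 | 6.0 | 0.15 | 0.15 |

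At the documented loss the gap appears at about one ninth of its size (519/58 = 8.9).

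**What each comparison could detect, for a 0.5 SD gap.** With 58 leavers and 461 stayers, the direct comparison has standard error √(1/461 + 1/58) = 0.139 SD. Since 0.5/0.139 − 1.96 ≈ 1.63, its power is about 95%. A two-sample test of all against stayers that ignored the overlap would use √(1/519 + 1/461) = 0.064 SD and would need a difference of about 1.96 × 0.064 = 0.125 SD, against an expected 0.056 SD. A simulation of 5,000 runs per setting gave these detection rates:

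| Lost | All v stayers, overlap ignored | Leavers v stayers |
|---|---|---|
| 58 | 0% | 95% |
| 104 | 8% | over 99% |
| 156 | 69% | over 99% |

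The article does not say that a test was used, so these rates only illustrate the contrast.

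**The denominator of the tenth.** The 58 refusals arose between the 2011 baseline and the 2012 follow-up, when the 2012 recruits were not at risk. If the 2011 wave made up a share w of the 519, loss among those at risk was 11.2%/w. The text does not give w. As assumed examples, w = 0.75 gives 14.9% and w = 0.5 gives 22.4%.

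**The case against.** The strongest reply is that the small difference is the right quantity for one purpose. The harm feared in a comparison of yearly averages is the shift in the average when leavers drop out, and that shift is exactly mean(all) − mean(stayers). For the characteristics compared, the check displays it undiluted. This stands: a small value does show that the measured averages moved little. It does not show that leavers resemble stayers, and it is silent on characteristics not compared and on change after baseline. A baseline comparison of leavers with stayers cannot settle the question of later change either, but it shows which patients were lost and what to adjust for.

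The second reply is that a difference in baseline level between leavers and stayers does not by itself bias within-person change. The section on data entry and analysis says the longitudinal structure will be taken into account when appropriate, and the sample size section refers to repeated measures in the same individual. This also stands, though no model is fixed. A reader might infer that selective loss will appear as programme benefit; the article does not establish that.

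Third, a reader might infer that the cohort is being treated as unselected, or that a reassuring result was bound to come out. The article says neither that loss is unrelated to outcome nor that any planned analysis rests on the check; it is one sentence of mild reassurance among the limitations. And at 30% loss the simulated detection of a 0.5 SD gap was 69%, so a reassuring result is close to automatic only at low loss.

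Finally, methods for missing data are commonly left to an analysis plan. Their absence from the article is not part of this point.

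**Conclusion.** The point holds as a limit on what the stated check can support. On its plain wording, the comparison shows the leaver/stayer difference multiplied by the fraction lost: 11.2% at the documented loss, and 20% to 30% under the assumed range. At low loss it can therefore say little about whether leavers resemble stayers. The figure of a tenth is arithmetically fair, but it understates loss in the wave that was at risk.

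The conclusion rests on three readings. The comparator was all baseline participants. Baseline values were used for both groups; if 2013 values were used for the later group, change over time is mixed in as well. And the 58 are a partial count, since they cover only refusals before the 2012 follow-up and total loss by 2013 may be larger. The sizes of the leaver/stayer gaps are illustrations, not estimates.

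The documents do not show that attrition was selective or that any result is biased, and no sample-size or power figure changes. What could change is the conclusion about attrition once the direct comparison is made.

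**What to change.** Replace the sentence with a direct comparison: 2013 participants against baseline participants absent in 2013, within recruitment wave, on baseline characteristics and baseline values of the primary outcomes. Give both numbers and standardised differences, and base the statement about attrition on that table. Report the 58 refusals against the number recruited in 2011 as well as against the total.

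For change over time, add a sensitivity analysis beside the unweighted result. It can use all available observations in a model that includes the baseline predictors of loss, or weights for the inverse probability of retention.

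The cost is a little analysis on data already held, and slightly wider intervals if weights are used.
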